### Income

[Ordered/Single/ two columns]

Q9 Please indicate which of these income bands come closest to your total gross annual income before tax and other deductions?

Answers

1. Less than £8,000
2. £8,000 to £12,999
3. £13,000 to £22,999
4. £23,000 to £33,999
5. £34,000 to £49,999
6. £50,000 to £66,999
7. £67,000 to £99,999
8. £100,000 to £134,999
9. £135,000+
10. Don't know
11. Prefer not to answer

### SES

[Ordered/Single/ two columns]

Q 10 Which of the categories below best describes your current employment?

Answers

1. Homemaker/ housewife
2. Retired
3. Unemployed/ on benefit
4. Factory/ manual/ unskilled worker
5. Crafts/ tradesperson/ skilled worker
6. Office/ clerical/ administration
7. Middle management
8. Senior management
9. Professional
10. Student/ full time education
11. Don't know

**SCREENED:**

- AGE: Under 30 and over 60 (Q1/1 or 4)
- IF BMI <30
- DIAGNOSED WITH HEART DISEASE, CANCER OR ANY OTHER CHRONIC DISEASE OF THE MAJOR ORGANS AT Q8 (CODE 2, 4 OR 5)
- OUT OF QUOTA

**Redirect: SSI thank you page (no payment)**

**QUOTAS (PER COUNTRY) / ASSIGN TO CELL:**

| HA+Planning              |                 | Heart-Age              |                 | Planning               |                 | Control Group          |                 |
|--------------------------|-----------------|------------------------|-----------------|------------------------|-----------------|------------------------|-----------------|
| Age                      | Gender          | Age                    | Gender          | Age                    | Gender          | Age                    | Gender          |
| 30-45
years
(N=50) | Males
(25)   | 30-45
years
(50) | Males
(25)   | 30-45
years
(50) | Males
(25)   | 30-45
years
(50) | Males
(25)   |
|                          | Females
(25) |                        | Females
(25) |                        | Females
(25) |                        | Females
(25) |
| 45-60
years
(N=50) | Males
(25)   | 45-60
years
(50) | Males
(25)   | 45-60
years
(50) | Males
(25)   | 45-60
years
(50) | Males (25)      |
|                          | Females
(25) |                        | Females
(25) |                        | Females
(25) |                        | Females
(25) |

## ELIGIBLE RESPONDENTS

### Page 3 – Next Steps

Thank you for helping with this survey. Now please click the 'Complete Survey' button below to close this profiling survey. You will then be taken to the Health Check Website which will tell you more about the research process.

#### qcells

[\[Single/Hidden\]](#)

Switch1      Alternatively directed to one of two cells?

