#### **1.4 Brief Description of Intervention**

The primary aim of the current study is to assess Heart-Age's motivational properties and its combined effects when used with planning on subjects' saturated fat intake.

Four sets of subjects will enter the online study site at three different times. In specific at **Time 1**, subjects will be invited to participate in the study by an online recruitment agency, which will also carry out the screening process. Once, subjects have been accepted in the study they will be asked to fill out three questionnaires: a) a self-reported dietary intake questionnaire, b) a self-reported questionnaire on various social-cognitive variables. At **Time 2**, which will be a week later, subjects will be randomly allocated into one of four conditions. In the most advanced condition subjects will go through the Heart-Age tool and then they will be asked to form a concrete plan on how to reduce saturated fat intake over the next two weeks. In the second and third conditions, subjects will be presented either with the Heart-Age tool or a planning session. There will be a control group, who will fill out questionnaires at pre-study, main study phase and post-study. At **Time 3**, subjects will be invited to fill-out again the same dietary measures of food intake and the questionnaire on the social-cognitive determinants. Study subjects will be rewarded for their participation in the study at Time 1 and 3 and will enter a prize draw of £200 in Amazon vouchers. This will be upon completion of study phase 3.

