## 3. Study Design

### 3.1. Design and Rationale

This is a randomised, between-groups study designed to assess the difference in saturated fat intake between four different experimental conditions; a) Heart-Age and Planning, b) Heart-Age, c) Planning and d) Control Group. Subjects will be randomly allocated to one of these conditions and their responses will be measured by self-reported questionnaires. Table 2 presents the breakdown of subjects in the different conditions. Allocation to the tools will be stratified to balance by age group (30-45 years or 46-60 years), and gender.

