### Phase 2 – Main study

In the main study phase, subjects will be randomly allocated into one of four different conditions: a) Heart-Age and Planning, b) Heart-age, c) Planning and d) Control Group. Those subjects going through Heart-Age will fill out a CVD assessment questionnaire. A paper copy version of the online questionnaire is found in Appendix 4. Once the CVD risk assessment questionnaire has been filled out then subjects will receive a Heart-Age score followed by brief advice on a number of lifestyle related aspects (Figure 2). Subjects in the planning condition will identify a list of situations where they would like to change their saturated fat intake. They will then be asked to match these situations with a list of behaviours. They would be requested to choose pairs of situations and behaviours that they want to change rather than ones that they are already doing (Appendix 5).

All subjects will be invited to answer a number of questions on their perceptions of the information received, intentions to make lifestyle changes, feelings of self-efficacy and expected outcomes. Subjects in the control group will only receive the questionnaires.

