## **11. Statistical Considerations**

### **11.1 Description of Statistical methods and interim analysis**

This is a randomised, stratified, between-groups study using a 2x2 factorial design with the factors 'use of the Heart-Age tool' and 'use of planning'. The primary endpoint is the change in saturated fat intake in participants allocated to the four different experimental conditions (Heart-Age and Planning, Heart-Age, Planning and Control Group). Participants will be randomly allocated to one of these four conditions, stratifying for age group (30-45 years or 46-60 years) and gender. Their saturated fat intake will be measured at baseline and the completion of the study (4 weeks after enrolment). The statistical analysis will compare the efficacy of the four treatment groups via the change in saturated fat intake between the baseline and final diet assessments. There will be no interim analyses.

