#### Answers

|                                  |   |
|----------------------------------|---|
| Cell 1 (Unilever to provide URL) | 1 |
| Cell 2 (Unilever to provide URL) | 2 |

Process thereafter

- 1. Respondents passed to Health Check Survey – Stage 1**
- 2. Respondents passed to Feedback Survey – Stage 2**
- 3. Respondents passed back to VSL Survey – Stage 3**

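### Appendix 6 contradicts the protocol body, and itself, on how many cells there are, when subjects are allocated and by what method

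*Protocol*

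**What the plan says.** **Protocol body.** Section 1.4 says that at Time 2, a week after Time 1, "subjects will be randomly allocated into one of four conditions". Section 5.1 (Phase 2) repeats this: "subjects will be randomly allocated into one of four different conditions". The study schematic also puts random allocation in Phase 2. Section 3.1 adds the strata: "Allocation to the tools will be stratified to balance by age group (30-45 years or 46-60 years), and gender". Section 11.1 agrees: "Participants will be randomly allocated to one of these four conditions, stratifying for age group (30-45 years or 46-60 years) and gender". Section 4.1 sets 100 subjects in each cell of a 2x2 factorial, and section 11.2 analyses it with a logistic model containing both factors and their interaction.

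**Appendix 6, the agency's screening script.** Two instructions bear on allocation:

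- The quota table is headed "QUOTAS (PER COUNTRY) / ASSIGN TO CELL". It lists all four arms by age and gender, with bands 30-45 and 45-60.
- After the eligibility screens, a hidden item named qcells reads "Alternatively directed to one of two cells". It offers two destinations, the second being "Cell 2 (Unilever to provide URL". The first step that follows is "Respondents passed to Health Check Survey – Stage 1". The list of later steps names three stages and no allocation.

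**The concern.** Section 5.1 names the Appendix 6 script as the one used to screen people, so a programmer will work from it. Followed literally, it gives two incompatible assignment instructions. Both come at the end of screening, before the Time 1 questionnaires, and neither mentions random allocation. The body requires four arms, randomised within strata, one phase later.

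Every efficacy comparison in section 11.2 depends on this step, and analysis cannot repair an allocation error. Three things are at stake: whether allocation is random and stratified, whether all four factorial cells are filled, and how much attrition falls after allocation.

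**Working it through.** **1. The texts side by side**

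| | Sections 1.4, 3.1, 5.1, 11.1 | Appendix 6 quota table | Appendix 6 qcells switch |
|---|---|---|---|
| Cells | 4 | 4 | 2, not mapped to arms |
| Timing | Time 2 (1.4, 5.1) | Screening | End of screening, before Stage 1 |
| Method | Random | Not stated | Apparently alternation |
| Strata | Age group and gender | Quotas by age and gender | None |
| Older band | 46-60 (3.1, 11.1) | 45-60 | None |

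**2. The plan's own targets reproduce**

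- Table 2 of section 3.1: 4 arms x 2 age bands x 2 genders x 25 = 400, or 100 per arm, as in section 4.1.
- Section 6.2: 900 recruited, 400 at the end, over two transitions. Retention per phase is r = sqrt(400/900) = 2/3, and 900 x (2/3)^2 = 400. The section speaks of a two-thirds drop-out, but that would leave 900 x (1/3)^2 = 100. One-third loss per phase is therefore inferred from the counts.

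**3. If the switch were the only allocation step**

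The section 11.2 model has four parameters: intercept, Heart-Age (H), planning (P) and H x P. The design rows (1, H, P, HP) are:

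- Heart-Age and Planning: (1, 1, 1, 1)
- Heart-Age: (1, 1, 0, 0)
- Planning: (1, 0, 1, 0)
- Control: (1, 0, 0, 0)

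With all four rows the matrix has rank 4, and both factors and the interaction are estimable. With any two rows (all six pairs were checked) the rank is 2, leaving the intercept and one contrast. For Heart-Age against Control, that contrast is the Heart-Age effect without planning. For Heart-Age and Planning against Control, it is the sum of both factor terms and the interaction, which cannot be separated. The 400 completers would fall as 200 + 200 instead of 4 x 100.

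**4. If the four arms were fixed at screening, as the quota table heading reads**

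Expected counts are 900 at Time 1, 900 x 2/3 = 600 at Time 2 and 600 x 2/3 = 400 at Time 3.

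- Allocation at Time 2: post-allocation loss (600 - 400)/600 = 33%.
- Allocation at screening: post-allocation loss (900 - 400)/900 = 56%.

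**5. Age 45**

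In the quota table, age 45 belongs to both bands. Table 2, sections 3.1 and 11.1, and the screener's own age coding all start the older band at 46.

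**The case against.** The strongest defence is that the design sections agree with one another and only an unfinished script departs from them. The script is labelled a draft, carries two version numbers and still awaits its URLs. Its two cells are never mapped to study arms, so they could be entry points to the study site, with four-arm randomisation following in Phase 2. Appendix 1 fits that: eligible subjects go to the main site, and conditions appear in Phase 2.

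This limits what can be claimed. A reader might infer that the switch is the only operational allocation instruction, and that the 2x2 factorial will therefore not be formed. The documents do not support that. The same script has a four-arm table, and nothing says that the switch replaces the Time 2 randomisation. Alternation is likewise the likely reading of the switch's wording, not an explicit rule. Even if the switch alternates, it is hidden and automated in a self-completed survey, and no recruiter is described who could exploit the sequence.

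The 56% figure also needs care. The Time 1 questionnaires are the same for everyone, so loss before Time 2 would precede any intervention, and the documents give no reason for it to differ by arm. The age overlap is a label slip, because the coded age variable puts 45 in one band only.

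The defence does not remove the contradiction. No text says that the two URLs are entry points. The four-arm table does not rescue the switch: the two disagree on the number of cells, and the table itself places assignment at screening.

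**Conclusion.** The point stands as an internal contradiction that must be resolved before the script is programmed. Appendix 6 disagrees with the body on timing, on method and on the older age band, and its switch and table disagree with each other on the number of cells.

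The size depends on which instruction is followed:

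- **Body followed:** there is no harm to the design.
- **Switch used as the allocation step:** allocation is unstratified, non-random if it alternates, and the planned model has rank 2 of 4.
- **Four arms assigned at screening:** post-allocation loss rises from about 33% to about 56%. This assumes equal one-third loss per phase, inferred from 900 to 400. It measures the attrition exposed after allocation and does not show bias.

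The loss of the factorial is thus one conditional outcome, not a result of the plan as a whole.

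**What to change.** - In Appendix 6, delete the two-cell switch and the assignment wording above the quota table. Keep the screener for age and gender quotas only.
- In sections 5.1 and 11.1, state that computer-generated 1:1:1:1 randomisation, stratified by age group and gender and carried out on the study site at Time 2, is the sole allocation step.
- Change 45-60 to 46-60 in the quota table.
- If two URLs are still needed as entry points, say so and state that they do not determine the arm.

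Block sizes and custody of the list can be left to a randomisation plan. The cost is a text edit and a programming check before launch, with no effect on subjects, sample size or duration.

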#### Answers

|                                  |   |
|----------------------------------|---|
| Cell 1 (Unilever to provide URL) | 1 |
| Cell 2 (Unilever to provide URL) | 2 |

Process thereafter

- 1. Respondents passed to Health Check Survey – Stage 1**
- 2. Respondents passed to Feedback Survey – Stage 2**
- 3. Respondents passed back to VSL Survey – Stage 3**

### Page 4 – Health Check Survey

#### Other Comments

[\[Open\]](#)

Q9      Do you have any other comments on the tasks carried out or the survey you have just completed?

*Please type your comments in the space provided.*
